## Discussion

This RCT will assess the effectiveness of the *Learn to be safe with Emmy and friends*™ program administered to first grade children in three regions in the state of Queensland, Australia. This program will be rigorously evaluated in the first multi-site cluster randomised controlled trial of a school-based child protection education program conducted in Australia. This child protection education program targets first grade children (aged 5–6 years), and draws on a set of core concepts identified in child protection and bullying prevention programs. Several key program outcomes will be assessed at multiple stages. We hypothesise that children’s short-term (T1 to T2) knowledge of program concepts,intentions to use program knowledge, skills, and help-seeking strategies, and actual use of program material in a simulated situation will increase. We also hypothesise that children will show long-term (T2 to T5) retention of these knowledge and skills. Children’swill also be measured to rule out any potential adverse effects of raising awareness of dangers and risk related to child protection issues. Other key program elements that will be assessed include parental discussion of material, parents’ observations of their children’s use of program materials, parents’ satisfaction with the program, and parental stress. The effectiveness of this program will also be evaluated for moderating effects, which will determine whether adaptations are required for different populations. Few experimental evaluations of a child protection education program have ever been reported in Australia (see [20], for an exception); this study, therefore, will fill an important gap in the child maltreatment prevention literature and will provide robust evidence of the benefits or otherwise of school-based child protection education programs in this context. The *Learn to be safe with Emmy and friends*™ program, while delivered selectively to volunteering schools at present, may have potential to become a more widely-used program should its effectiveness be determined.

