**Methods/Design:**

A three-site cluster randomised controlled trial (RCT) of Learn to be safe with Emmy and friends™ will be conducted with children in approximately 72 first grade classrooms in 24 Queensland primary (elementary) schools from three state regions, over a period of 2 years. Entire schools will be randomised, using a computer generated list of random numbers, to intervention and wait-list control conditions, to prevent contamination effects across students and classes. Data will be collected at baseline (pre-assessment), immediately after the intervention (post-assessment), and at 6-, 12-, and 18-months (follow-up assessments). Outcome assessors will be blinded to group membership. Primary outcomes assessed are children’s knowledge of program concepts; intentions to use program knowledge, skills, and help-seeking strategies; actual use of program material in a simulated situation; and anxiety arising from program participation. Secondary outcomes include a parent discussion monitor, parent observations of their children’s use of program materials, satisfaction with the program, and parental stress. A process evaluation will be conducted concurrently to assess program performance.

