### Recruitment and participants

The study will be conducted in first grade classrooms with children aged 5–6 years in three education regions in Queensland, Australia: Brisbane (Metropolitan Region, urban schools), Gold Coast (South East Region, urban schools), and Townsville (North Queensland Region, rural schools). Eightschools in each region will be randomly selected to participate. Trained research assistants not involved in data collection will initially contact schools. An information sheet detailing the *Learn to be safe with Emmy and friends*™ program and explaining the evaluation will be sent to school principals who will be asked to provide consent for their school’s participation. Randomisation will be conducted following principal consent, after which time, schools will be asked to distribute standardised information sheets with consent forms (either waitlist-control or intervention version) to parents/guardians (hereafter, parents) of all children enrolled in first grade. Parents return consent forms to the school if they agree for their child to participate.

A simple random sampling strategy with individuals as the primary sampling unit was assumed, and G*Power was then used to estimate sample size. This returned a suggested total sample size of at least 100 children per group at each of three sites. Based on similar studies [22] that have used cluster sampling with schools as the primary sampling unit, the sample size with this design effect was estimated to be approximately 1.5, taking into account potential attrition of (20 %) owing to student absences and/or mobility. In addition, enough power will be needed to examine the effects for subgroups (sex/school/family/stress, etc.). Therefore, a total sample size of at least 1350 is required in this study to test the effectiveness of the intervention. Assuming conservative class sizes of 20 students per class (60 children per school; 9 schools in each region), a final initial sample size of 1620 Year 1 children and their parents is planned to give sufficient power for this study.

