#### Demographics

Family and child demographic information will be collected in 10 items including child gender, child age, parental gender, parental age, family structure, parental income and parental education. In these items family community engagement and the child’s social and school engagement will also be assessed.

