### Planned analyses

Mixed factorial analyses of variance (ANOVAs) will be used to examine the effectiveness of the program for primary outcomes. Analyses will be conducted to assess differences between the intervention and waitlist control conditions over time using 2 (Group: intervention, waitlist-control) x 3 (Time: T1, T2, T3) mixed ANOVAs. Primary or target outcomes include children’s knowledge of program concepts, intentions to use program knowledge, skills, and help-seeking strategies, and anxiety as a result of program participation. T-tests will be conducted to examine the difference between groups in use of program skills and disclosure during the simulated situation conducted at T2 and T3.

Following the 6-month follow-up of the children who received the program, data will be analysed to assess stability of improvement in the treatment group from post to, 6-, 12- and 18-month follow-up. One-way ANOVAs will also be conducted for these variables for the intervention group across the five time points (T1, T2, T3 and T4, T5).

Hierarchical linear modelling [37] will be used to examine any effects of the hierarchical structure of the study design. If there are hierarchical effects, this analysis will be used to account for influences of classroom (level 2) and school level effects (level 3), while examining the effects of condition (Emmy/waitlist) and within student changes over time. Regression will be used to test the mediation analyses and to examine any effects of moderators (e.g. demographic variables, parental stress, dose–response) to determine which factors may differentiate intervention effects. Intent-to-treat analyses will also be conducted to account for potential effects of differential drop-out.

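### The Discussion lets moderator analyses decide whether the program must be adapted, but the plan describes an open search with no stated subgroup effect or power; the analyses should be called exploratory

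*Protocol article*

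**What the plan says.** Three places in the protocol article bear on this.

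- **Discussion.** The role of the analyses is stated as: "The effectiveness of this program will also be evaluated for moderating effects, which will determine whether adaptations are required for different populations".
- **Planned analyses.** Regression is to be used "to examine any effects of moderators (e.g. demographic variables, parental stress, dose–response) to determine which factors may differentiate intervention effects". The list is given by example only. Hierarchical modelling appears in the same paragraph, but for the effect of condition and change over time; the moderator work is assigned to regression.
- **Recruitment and participants.** The article says that "enough power will be needed to examine the effects for subgroups (sex/school/family/stress, etc" (the list is again left open) and then concludes that at least 1350 children are required. It gives no subgroup effect size, power or calculation.

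The number of candidates is not stated. Demographics says: "Family and child demographic information will be collected in 10 items including child gender, child age, parental gender, parental age, family structure, parental income" among others, with community, social and school engagement also covered. The outcomes differ by place. Planned analyses has three for the main models ("Primary or target outcomes include children’s knowledge of program concepts, intentions to use program knowledge, skills, and help-seeking strategies, and anxiety"). The abstract adds a fourth, "actual use of program material in a simulated situation; and anxiety arising from program participation".

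**The concern.** The Discussion turns the moderator analyses into the basis for a decision about the program, while the analysis section describes a search for whatever factors may matter. A search of that kind can mislead in two ways. A chance interaction can be read as proof that some population needs a different version of the program. A non-significant interaction can be read as proof that the program suits everyone as it stands. The article foresees wider use of the program if it proves effective, so either misreading could affect how it is delivered. The sample-size paragraph adds to the risk by suggesting that subgroup effects are powered.

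**Working it through.** **1. Does the stated sample size contain a subgroup calculation?**

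- Base: 100 per group x 2 groups x 3 sites = 600.
- With the factor of 1.5, which the text appears to say already includes 20% attrition: 600 x 1.5 = 900.
- With attrition added separately: 900 / 0.8 = 1125, or 900 x 1.2 = 1080.
- None of these gives 1350. From 900, 1350 needs a further factor of 1.5 (600 x 1.5 x 1.5), which is not explained.

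The planned total of 1620 is 27 schools x 60. The 24 schools named elsewhere would give 24 x 60 = 1440. Whatever the subgroup step was, the article does not show it.

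**2. False signals if no moderation exists.**

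Assumptions, none of them in the article: separate tests, two-sided 0.05, no correction. For k moderators and q outcomes, if independent, P(at least one) = 1 - 0.95^(kq).

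| Moderators x outcomes | Basis | Probability |
|---|---|---|
| 4 x 2 | four named subgroups; anxiety left out as a harm check | 1 - 0.95^8 = 34% |
| 5 x 3 | illustration | 1 - 0.95^15 = 54% |
| 10 x 3 | ten demographic items, three outcomes | 1 - 0.95^30 = 79% |
| 10 x 4 | same, with the abstract's fourth outcome | 1 - 0.95^40 = 87% |

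Correlation lowers these figures. By simulation for 10 x 3, outcome correlation 0.3 with moderator correlation 0 to 0.3 gives 71-77%. Outcome correlation 0.7 with moderator correlation 0.5 gives 53%. Dose-response is left out of the counts: waitlist schools receive no program until after the six-month assessment, so it is not an ordinary arm-by-moderator test.

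**3. What a non-significant result can show.**

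Region serves as the example because Recruitment and participants calls Townsville rural and the other two regions urban.

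- Schools: 8 per region. With 1:1 allocation within region (assumed), 4 v 4 rural and 8 v 8 urban.
- Children per school: 60, from the article.
- School-mean variance in SD units: v = ICC + (1 - ICC)/60.
- Standard error of the difference in effects: SE = sqrt(2v/8 + 2v/4) = sqrt(0.75v).
- Test: noncentral t, 20 df, two-sided 0.05, no baseline adjustment.
- ICC: a design effect of 1.5 implies (1.5 - 1)/(60 - 1) = 0.0085, lower if the 1.5 also covers attrition. The other ICCs are assumptions.

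| ICC | v | SE | Power, 0.3 SD | 0.4 SD | 0.5 SD |
|---|---|---|---|---|---|
| 0.0085 | 0.0250 | 0.137 | 55% | 79% | 93% |
| 0.02 | 0.0363 | 0.165 | 41% | 64% | 82% |
| 0.05 | 0.0658 | 0.222 | 25% | 40% | 57% |
| 0.10 | 0.1150 | 0.294 | 16% | 25% | 37% |

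If baseline adjustment removed 36% of the variance (assumed), power at 0.3 SD would be 74% at ICC 0.0085 and 36% at 0.05. With 27 schools and no adjustment, power at 0.3 SD and ICC 0.05 is 28%.

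**4. Would a multiplicity correction rescue the claim?**

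Bonferroni over 30 tests (0.05/30 = 0.00167) holds the false-signal rate at 4.9% if independent. Power for the regional contrast at 0.3 SD then falls to 11% at ICC 0.0085 and 3% at 0.05. Correction protects one direction of the decision and weakens the other.

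**The case against.** The strongest reply is that the article contains no decision rule. It gives no alpha for moderators, does not say that any significant interaction triggers adaptation, and does not say that a null result means none is needed. Planned analyses is more cautious than the Discussion, speaking of factors that may differentiate effects. A closed list and a multiplicity method are commonly left to the statistical analysis plan, which is not shown. All of this stands. A reader might infer a built-in rule that raises a false alarm in 70-80% of null trials. The documents do not support that: the figure needs about ten separate, uncorrected tests per outcome, and smaller counts or strong correlation give much less.

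A reader might also infer that the trial will often miss an urban/rural difference. Region is not named as a moderator, and rural means a single region, so the contrast is equally one of Townsville against the rest. At the ICC implied by the plan's own design effect, power for 0.4-0.5 SD is adequate (79-93%), and baseline adjustment would raise it. Low power is confined to smaller differences or larger ICCs.

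What the reply does not remove is the Discussion sentence. An analysis plan could tidy the testing, but the published claim would still give these analyses a deciding role that no stated design input supports.

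**Conclusion.** The point holds as a mismatch between claim and design. The article says that the moderator analyses will settle whether adaptations are needed. What it describes is an open search, with subgroup power asserted and not calculated. The false-signal figures in step 2 are conditional on separate uncorrected tests at 0.05 and on counts that the article does not fix; they show scale and are not properties of the plan. The regional figures show only that a null interaction could coexist with a 0.3-SD difference in effect. They rest on 1:1 allocation, 60 children per school, no baseline adjustment and, above 0.0085, assumed ICCs. The absence of a closed list or a correction method is not part of the finding.

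**What to change.** In Planned analyses, state that moderators will be tested as arm-by-moderator interactions within the hierarchical model, so that school-level moderators are judged against school-level error, and that each interaction will be reported as an estimate with a 95% confidence interval. Label the moderator analyses exploratory, and state that a non-significant interaction will not be read as showing that no adaptation is needed. In the Discussion, replace the statement that these analyses decide whether adaptations are required with one that they explore whether effects differ between populations.

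The cost is wording in the analysis section and the Discussion; design and data collection are unchanged. The trial gives up a definitive claim about adaptations.
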